##### Pain

Pain will be evaluated by pressing on the different trigger points. This will require an algometer that can evaluate the pressure exerted on these points, such as the Force Ten FDX (Wagner Instrument). The evaluator will have undergone measurement training prior to the initial measurements [50]. In addition, each participant will be asked about their pain using an Analog Visual Pain Scale [51,52] at baseline, at the end of the treatment and follow up; as well as before and after each training.

##### Health-Related Quality of Life (HRQoL)

Health-related Quality of Life will be evaluated using the following questionnaires:

*15-D.* A 15-dimensional questionnaire (Cronbach’s alpha = 0.79) with 5 degrees of response in each dimension. For its result, it contains a final measure from 0 to 1, where 0 is the worst possible quality of life and 1 is the best. This questionnaire is based on preferences for what allows cost-effectiveness analysis [53,54].

*SF-12.* A 12-question tool (Cronbach’s alpha > 0.70), an abbreviated version of the SF-36 questionnaire, results in 8 dimensions (physical function, physical role, body pain, general health, vitality, social function, emotional role, mental health) and 2 summary components (physical and mental). These dimensions, as well as the components, score from 0 to 100, where 0 is the worst state of health and 100 the best. This questionnaire allows the obtainment of a utility index, including the SF-6D, which is contained within it. The index from SF-6D is comprised between 0 and 1, where 0 is the worst possible state of health and 1 the best [55].

*HUIv3.* This questionnaire consists of 8 dimensions with 5 or 6 possible response levels depending on the dimension (Cronbach’s alpha = 0.79). The dimensions are: Vision, hearing, speech, wandering, dexterity, emotion, cognition, and pain. The score ranges from 0 to 1, with 0 being the worst possible state of health and 1 being the best [56]. The Verran Snyder–Halpern sleep scale [57] will also be used, as well as a visual analogue sleep scale [58].

##### Incapacity in Fibromyalgia

Two different questionnaires will be applied: The Fibromyalgia Impact Questionnaire (FIQ) and the Revised Fibromyalgia Impact Questionnaire (FIQ-R).

*Fibromyalgia Impact Questionnaire (FIQ).* This questionnaire consists of 20 questions, the first 10 belonging to a single dimension. The total score of the questionnaire is between 0 and 100, with 0 being no disability due to FM and 100 being the maximum disability due to FM [59].

*Revised Fibromyalgia Impact Questionnaire (FIQ-R)* [60,61]. This questionnaire contains 21 items that mention symptoms or problems you have had in the last 7 days with a response scale ranging from 0 to 10, where 0 is the absence of the problem and 10 is the greatest intensity of the problem. The FIQ-R consists of 3 domains: “Function” (first 9 items), “Global Impact” (two items), and “Severity of symptoms” (10 items). The main difference with the FIQ is that the third domain includes 4 new aspects related to memory, sensitivity, balance, and sensitivity to loud noises, bright lights, smells, and cold temperatures. In addition, the scoring system also has several advantages. This questionnaire has been shown valid and reliable (Cronbach’s alpha = 0.93) [60].

##### Depression

The depressive symptoms of FM patients will be evaluated as one of the commonly associated symptoms. The Beck Depression Inventory second edition (BDI-II) is a 21-item self-report instrument designed to assess the severity of depressive symptomatology in adults and adolescents, with a minimum age of 13 years (Cronbach’s alpha = 0.94) [62]. In each of the items, the person must choose, from a set of four alternatives ordered from least to most severe, the sentence that best describes his/her state during the last two weeks, including the day when he/she completes the instrument. In terms of correction, each item is scored from 0 to 3 points depending on the alternative chosen and, after directly adding up the score of each item, a total score ranging from 0 to 63 can be obtained. Sometimes it is the case that the person chooses more than one alternative in an item given. In this case, the punctuation of the chosen phrase is taken more seriously. Several studies on psychometrics guarantee the reliability and validity of the BDI-II in very diverse samples [62,63].

##### Happiness

Happiness will be assessed using the General Happiness Scale (Cronbach’s alpha = 0.86) [64] and the Satisfaction with Life Scale (SWLS) (Cronbach’s alpha = 0.78) [65], which will be applied before, during, and after treatment.

##### Physical Activity and Sedentary Behaviors

*Physical activity in leisure time.* The Leisure Time Physical Activity Instrument (LTPAI) will be used to assess the physical activity performed by participants in their leisure time (ICC = 0.84) [66]. This questionnaire consists of 4 items with 3 activity levels: Light, moderate, and vigorous (a short description of each category will be presented). Subjects will be asked to recall the average number of hours a week during the previous 4 weeks that they had spent engaged in physical activity and at what activity level. The scale will be simplified into the following 3 levels: (1) 0.5 to 1.5 h a week, (2) 2 to 4 h a week, and (3) more than 4 h a week, and the respondent will be asked to provide answers in hours. For the first 2 activity levels, the mean number of hours (1 and 3 h, respectively) will be used to calculate the total score. If no level will be selected for a category, the number of hours will be assigned a value of 0 for that category. The number of hours will indicate by the subjects for each intensity category will be summed to obtain the leisure-time physical activity level for 1 week [66].

*Physical Activity at Home and Work.* The Physical Activity at Home and Work Instrument (PAHWI) will be used (ICC = 0.87) [66]. This questionnaire consists of 7 items with 3 categories for work performed at home (light, moderate, heavy activity) and 4 categories for employment (sedentary, light, moderate, heavy activity). A short description of each category will be presented, and the respondents will be asked to report the amount of time spent performing each of the activity categories. The hours for each category will be summed to obtain the total score for the PAHWI (activity at housework and activity at the workplace) [66].

*Sedentary Behavior Questionnaire (SBQ).* This test assesses the amount of time spent on 11 behaviors (ICC = 0.85) [67]. The 11 items will be completed separately for weekdays and weekend days. Response options are: “None”, “15 min or less”, “30 min”, “1 hour”, “2 h”, “3 h”, “4 h”, “5 h”, or “6 h or more”. The time spent on each behavior will be converted into h (e.g., a response of 15 min will be recorded as 0.25 h) [67,68]. For the total scores of sedentary behaviors, hours per day for each item will be summed separately for weekday and weekend days. To obtain weekly estimates, weekday hours will be multiplied by 5 and weekend hours will be multiplied by 2, and these will be summed for total hours/week. For the summary variables of total hours/day spent in sedentary behaviors (weekday and weekend) and total sedentary hours/week, responses higher than 24 h/day will be truncated to 24 h/day.

##### Clinical Global Impression

Improvement due to interventions will be measured using the Patient Global Impression of Improvement Scale [69], which uses the Likert scale.

##### Tests Familiarization and Reliability

Before each session, there will be a warm-up phase where the participant will have the test procedure explained, including the specific test trial, before it will be carried out.

The different tests inter-session reliability will be evaluated by repeating the tests two weeks after with part of the sample participants. All possible tests will be carried out under single and dual-tasks conditions.

### 2.8. Statistical Analysis

Baseline characteristics of participants will be presented as the mean (standard deviation) for continuous variables and proportions for categorical variables. The normality will be checked using the Kolmogorov-Smirnov test. Then, two types of analyses will be performed: 1) An intention-to-treat analysis including all participants and 2) a per-protocol analysis using only those participants who complete the study.

**Intention-to-treat analysis.** This analysis will include all randomly assigned participants in their corresponding groups. Multiple imputations will be used to impute lost data. The effects of the intervention on the main and secondary variables will be computed using a repeated measures ANCOVA test, adjusted by age and baseline values. Results shall include the Cohen’s *d* effect size (95% confidence interval) and statistical significance for each dependent variable respect to time and its interaction effects (group × time). Statistical significance shall be established at the conventional level of *p* < 0.05. In sensitivity analyses, the data imputation will be made from the baseline patient data and from those participants who completed the study, in order to avoid estimation biases. 

**Analysis by protocol.** Similar analyses than those described above will be carried out, but only using participants who have attended at least 75% of the sessions.

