## Abstract

Background: Women with fibromyalgia (FM) have 2.5 falls per year compared to the 0.5 falls in people without FM. This fact poses a significant health expense. Square Stepping Exercise (SSE) is a balance training system that has been shown to be effective in preventing falls in the elderly. However, there are neither studies in people with FM nor studies that apply SSE through video-conferencing (Tele-SSE). The objectives of this project are 1) to investigate the applicability, safety, decrease in the number of falls, and incremental cost-effectiveness ratio of prevention of falls program through Tele-SSE in women with FM, and 2) to study the transfer of obtained results to the public and private socio-health economy of Extremadura. Methods/Design: A randomized controlled trial with experimental (Tele-SSE) and control (usual treatment) groups will be carried out. The application of Tele-SSE will be performed for 12 months (three times per week) and one additional follow-up month after the intervention. A focus group including agents to identify key points to transfer the findings to the public and private sectors in Extremadura. One-hundred and eighteen women with FM will be recruited and randomly distributed into the two groups: Experimental (Tele-SSE; *n* = 59) and control group (Usual care; *n* = 59). Primary outcome measures will be: 1) Applicability; 2) safety; 3) annual number of falls; and 4) incremental cost-effectiveness ratio. Secondary outcomes will be: 1) Balance; 2) fear of falling; 3) socio-demographic and clinical information; 4) body composition; 5) physical fitness; 6) physical activity and sedentary behavior; 7) quality of life-related to health, mental health, and positive health; 8) pain; 9) disability level; 10) cognitive aspects; and 11) depressive symptoms. Regarding the focus group, the acceptability of the Tele-SSE will be evaluated in social-sanitary agents and will include Tele-SSE in their services offer. A statistical analysis will be carried out by treatment intention and protocol. In addition, a cost-effectiveness analysis from the perspective of the health system will be performed. Discussion: This project aims to improve the efficiency and equity of physical therapy services based on tele-exercise in preventing falls in people with FM. Furthermore, orientations will be given in order to transfer the obtained findings into the social-sanitary system and market.

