Fibromyalgia (FM) is a chronic syndrome that affects 3.43% of women worldwide, 3.90% in Europe, and 4.2% in Spain [14]. This syndrome has a considerable functional impact on people who suffer from it, as they present chronic pain problems requiring many social, health, and work resources through comprehensive and continuous care [15]. It is estimated that people with FM represent an annual expense of 11,629.03 euros per patient and year in Spain, costing a total of 4223.02 million euros to Spanish health services, which poses a 279.10-euro cost per inhabitant and year [14]. If we consider that, according to the Ministry of Health of Extremadura, a health expenditure of 1549 euros per inhabitant was made in 2016, the expense on fibromyalgia represents 18% of the total health cost per inhabitant in Extremadura. Therefore, any intervention that may help to reduce these percentages could have a positive impact on reducing the costs of the Extremadura health system.

Falls in people with FM amount to 2.5 per year compared to 0.5 for people without FM [16]. Thus, part of the annual health costs of this syndrome comes from falls. The project that we are presenting attempts to reduce costs associated with falls in this population through balance training with the SSE method, conducted by a professional through video-conferencing (Tele-Square Stepping Exercise; Tele-SSE), improving the balance and preventing falls in women with FM. Reviewing the scientific literature, the SSE program appears to improve balance by preventing falls and decreasing the fear of falling in older adults [13], but no publication had studied the benefits of SSE in people with FM.

Therefore, the main objectives of this project are 1) to investigate the applicability, safety, decrease in the number of falls, and incremental cost-effectiveness ratio of a prevention of falls program through Tele-SSE in women with FM, and 2) to identify key factors for its transfer to the public and private social health system, evaluating the acceptability of Tele-SSE in the agents of the social health system in charge of including Tele-SSE in their services offer.

Additionally, this project has a secondary aim to evaluate the effect of Tele-SSE on balance levels, fear of falling, body composition, physical fitness, quality of life related to health and positive health, pain, disability level, depressive symptoms, and cognitive aspects of participants.

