#### 2.7.1. Randomized Trial Main Measures

**Applicability.** The percentage of participants with FM who can perform the proposed training. If any participant is unable to perform the intervention, the cause will be noted.

**Safety.** A record shall be kept about any incidence, injury or problem during the sessions, as well as if possible, the origin of the problem.

**Number of falls in the last year and six months.** Participants will be asked about the number of falls that they have suffered in the past year and six months. The World Health Organization (WHO) definition of falls will be adopted, namely: “Involuntary events that cause the body to lose its balance and find itself on land or on another firm surface that stops it”.

**Incremental cost-effectiveness ratio.** The average cost of the intervention and the effects on health will be calculated for both intervention and control groups. The measurement of health effects is defined as Quality Adjusted Life Years (QALYs), which is calculated by multiplying the life years (life expectancy) with the quality of life of the participants [25]. The health-related quality of life will be evaluated using the EQ-5D-5L questionnaire [26] and this measure will be used for sample calculation. Incremental cost-effectiveness ratio will be calculated by dividing the difference between the average costs of both groups by the difference in mean QALYs gained in both groups. The utilities needed to calculate the QALYs will be computed for each set of health status using the algorithm available on the official website of the EuroQol group (http://www.euroqol.org/). The algorithm used to calculate the EQ-5D-5L utility index will be the “crosswalking” of the EuroQol levels Spanish version. This utility index is comprised between −0.654 (corresponding to the worst state of health and equivalent to 55555) and 1 (perfect state of health and equivalent to 11111).

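### Cohen's d from a repeated measures ANCOVA cannot state the reduction in falls, a primary count outcome; a rate ratio from a count model would

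*Protocol article*

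**What the plan says.** The Abstract lists the primary outcomes as "1) Applicability; 2) safety; 3) annual number of falls; and 4) incremental cost-effectiveness ratio". Section 2.7.1 describes how falls are obtained: "Participants will be asked about the number of falls that they have suffered in the past year and six months". Table 2 schedules this question at baseline and at months 6, 12 and 13.

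Section 2.8 gives one method for all outcomes: the "effects of the intervention on the main and secondary variables will be computed using a repeated measures ANCOVA test", with age and the baseline value as covariates. The results are to include Cohen's d, specified as "effect size (95% confidence interval) and statistical significance for each dependent variable respect to time and its interaction effects". The section also says "The normality will be checked using the Kolmogorov-Smirnov test", but names no other method if that check fails. The intention-to-treat analysis keeps every randomised woman and fills lost data by multiple imputation. No count model, time-at-risk term, fall rate or rate ratio is mentioned.

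The Background supplies the only fall rate in the document: "Falls in people with FM amount to 2.5 per year compared to 0.5 for people without FM".

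**The concern.** The first main objective includes showing fewer falls, and section 2.9 carries the effect on falls into the economic analysis. Both need a figure that a reader can take as falls avoided or as a proportional reduction.

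An annual fall count is discrete and right-skewed. Some women will report none and a few will report many. Its variance moves with its mean, so an effective programme makes the two arms' variances differ. Cohen's d divides the mean difference by a pooled SD that depends on the dispersion between women and on the treatment effect itself. The same d can therefore stand for quite different reductions, and the same reduction can give quite different values of d. This is not a detail left to an analysis plan: the article fixes both the model and the effect measure, and the effect measure does not suit this outcome.

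**Working it through.** **The plan's own figure.** The sample size of 118 reproduces, but it rests on EQ-5D-5L: 2 × (1.960 + 0.842)² × 0.26² / 0.15² = 47.16 per arm, and 47.16 / 0.80 = 58.95, so 59 per arm. It carries no information about falls.

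**Inputs.** Mean 2.5 falls per year (Background), 59 per arm and 20% loss (section 2.3). The dispersion k and the rate ratio RR are not in the document. I assume k = 0.5, 1 and 2 and RR = 0.7 and 0.6.

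**Spread of the count.** For a negative-binomial count with mean m, variance = m + k m² and P(no falls) = (1 + k m)^(−1/k). At m = 2.5:

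| k | Variance | SD | No falls |
|---|---|---|---|
| 0.5 | 5.6 | 2.4 | 20% |
| 1 | 8.75 | 3.0 | 29% |
| 2 | 15 | 3.9 | 41% |

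At k = 1 and RR 0.6 the treated mean is 1.5 and its variance is 1.5 + 1.5² = 3.75, against 8.75 in controls.

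**What d = 0.3 means.** Take d = (m0 − m1) / √((V0 + V1)/2), with m0 = 2.5 and m1 = 2.5 × RR:

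- k = 0.5, RR 0.74: m1 = 1.85, V1 = 3.56; 0.65 / √4.59 = 0.30
- k = 1, RR 0.69: m1 = 1.725, V1 = 4.70; 0.775 / √6.73 = 0.30
- k = 2, RR 0.61: m1 = 1.525, V1 = 6.18; 0.975 / √10.59 = 0.30

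So one value of d covers reductions of 26%, 31% and 39%. In the other direction, RR 0.6 gives d = 0.49, 0.40 and 0.31 for k = 0.5, 1 and 2.

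**Error rates and power.** The simulation has 59 per arm and 600 runs per cell. All leavers (20%) go after the month-6 count, and each woman's underlying rate is the same before and after randomisation apart from treatment. A single ANCOVA of the annual total, adjusted for baseline falls but not age, stands in for the repeated measures model.

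| k | RR | ANCOVA with multiple imputation | Negative binomial with offset | Gap (points) |
|---|---|---|---|---|
| 0.5 | 1 | 5.3% | 6.4% | – |
| 1 | 1 | 4.0% | 4.7% | – |
| 2 | 1 | 4.8% | 6.2% | – |
| 0.5 | 0.7 | 53.8% | 55.9% | 2.1 |
| 1 | 0.7 | 51.2% | 55.0% | 3.8 |
| 2 | 0.7 | 48.8% | 52.2% | 3.4 |
| 0.5 | 0.6 | 83.0% | 83.3% | 0.3 |
| 1 | 0.6 | 78.3% | 80.5% | 2.2 |
| 2 | 0.6 | 78.2% | 78.5% | 0.3 |

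The simulation error near 50% is about √(0.5 × 0.5 / 600) = 2 points, so part of each gap may be noise. A few negative-binomial fits failed (586 to 599 of 600 usable per cell). Repeating the comparison with a baseline-to-follow-up correlation of 0.5 lowered power for both models and left gaps of the same order.

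**The case against.** The strongest defence is that the ANCOVA is not a wrong test. Allocation is 1:1, type I error is close to nominal, and the planned imputation brings its power close to that of the count model. A check of the adjusted mean difference (47 completers per arm, the same assumed dispersions, RR 1 and 0.6, 4,000 runs) found 95% CI coverage of 94% to 95.5%. That difference, in falls per woman-year, is itself a valid answer to the objective. Section 2.8 says what results must include and does not forbid means and differences. All the variance figures rest on an assumed dispersion.

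Most of this stands, and it rules out three stronger readings that a reader might infer:

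- **Partial follow-up is thrown away.** The intention-to-treat analysis keeps all randomised women, and a month-6 count can inform an imputed month-12 count. On the Table 2 schedule, a woman who leaves before month 6 has no post-baseline count, so an exposure offset could not recover her data either.
- **Power is materially lost.** Gaps of about 11 points (50% against 61.5%, and 30.5% against 42%) appear only when the comparator is ANCOVA in completers, which is not the planned intention-to-treat analysis.
- **The p-value or the interval for the mean difference is invalid.** The simulations do not show this.

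What the defence does not answer is that the only effect measure the plan commits to is Cohen's d, which does not identify the reduction in falls. A mean difference might be reported, but nothing requires it.

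**Conclusion.** The point holds as a problem of model and effect measure for one primary outcome. With 2.5 falls per year and an assumed dispersion of 0.5 to 2, d = 0.3 can mean a rate ratio anywhere from about 0.74 to 0.61, so the planned summary cannot state the decrease in falls that the trial sets out to show. The plan also has no exposure term and relies on imputing counts for a Gaussian model, but the cost in error rate and power is small: about 0 to 4 points under the stated simulation assumptions. The dispersion and rate ratios are assumptions; the direction of the argument needs only that the fall count's variance rises with its mean. Severity: should fix.

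**What to change.** For falls only, replace the ANCOVA in section 2.8 as follows.

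- **Outcome window:** falls from randomisation to month 12, built from the six-month recalls at months 6 and 12, which do not overlap. Do not use the past-year recall at month 6, because it reaches back before randomisation.
- **Model:** negative-binomial regression with group, age and baseline falls as covariates (baseline as log(falls + 0.5), for example) and log of the observed recall time as offset.
- **Report:** falls per person-year by arm and the incidence rate ratio with 95% CI, with robust standard errors as a check.
- **Missing counts:** women with no post-baseline count stay under the planned multiple imputation.

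Keep ANCOVA and Cohen's d for the continuous outcomes.

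The cost is a change of wording, with no new visit, instrument or participant. The downside is that likelihood standard errors may be slightly small at 59 per arm (simulated null rejection 4.7% to 6.4%), which is why the robust check is included. The change should be made before unblinding, so that it cannot look data-driven.

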### 2.3. Sample Size

The number of participants was calculated based on the change in quality of life assessed using the 5-level Euroqol-5D questionnaire (EQ-5D-5L). As far as we know, there are no available data on the minimum real change in the EQ-5D-5L in fibromyalgia patients, so we have used a reference of pathology that deals with pain, being this real minimum difference of 0.15 [19]. Therefore, a total of 118 participants (Experimental group; *n* = 59 and Control group; *n* = 59) are needed; accepting alpha and beta risks of 0.05 and 0.2, respectively, in a bilateral contrast, to detect a difference equal to or greater than 0.15 units. It is assumed that the common standard deviation of EQ-5D-5L is 0.26, taking as a reference one of the articles by the principal investigator of this project, which evaluated the health-related quality of life through this questionnaire [20]. A follow-up loss rate of 20% has been estimated. 

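### The repeated measures ANCOVA adjusts for baseline but names significance only for time and group × time, so a stable benefit could be reported as non-significant

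*Protocol article*

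**What the plan says.** Section 2.8 (Intention-to-treat analysis) applies one model to all main and secondary variables: a repeated measures ANCOVA "adjusted by age and baseline values". The results are to include Cohen's d with a 95% confidence interval and "statistical significance for each dependent variable respect to time and its interaction effects", the interaction being group × time, at p < 0.05. The contrast behind Cohen's d is not stated. Neither a group effect nor a difference between arms at a given visit is named. The text does not say whether baseline is also a level of the time factor.

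Section 2.3 sizes the trial on EQ-5D-5L, with alpha 0.05 and beta 0.2 "in a bilateral contrast, to detect a difference equal to or greater than 0.15 units". It assumes that "the common standard deviation of EQ-5D-5L is 0.26" and adds: "A follow-up loss rate of 20% has been estimated". The result is 59 per arm, 118 in total.

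Table 2 places most outcomes at baseline and months 3, 6, 9, 12 and 13. EQ-5D-5L has no row of its own. The cost-effectiveness row, which uses it according to section 2.7.1, is marked at baseline, month 12 and month 13.

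**The concern.** When the baseline value is a covariate and the follow-up visits are the outcomes, the treatment effect sits in the group term or in the group difference at a chosen visit. Group × time then asks a narrower question: does the difference between arms change across follow-up visits? If Tele-SSE helps by the first follow-up visit and the gain is held, the honest answer is no, and the interaction is not significant. If EQ-5D-5L is analysed at months 12 and 13 only, the interaction asks whether the effect changed in the month after training ended. The time effect pools both arms and says nothing about Tele-SSE against usual care.

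The trial was sized for a difference between arms. If the p-values reported are those that section 2.8 lists, a real benefit of the planned size could be published as no significant interaction.

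**Working it through.** **Inputs from the documents:** difference 0.15, SD 0.26, two-sided alpha 0.05, power 0.80, loss 20% (section 2.3); visits from Table 2. **Assumed:** equal correlation ρ between all visits, taken as 0.3, 0.5 and 0.7, because the documents give none. Age is left out of the calculation; it costs one degree of freedom.

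**1. The plan's own figure.** n per arm = 2 × (1.96 + 0.84)² × 0.26² / 0.15² = 47.16 with unrounded normal quantiles. Allowing for loss, 47.16 / 0.8 = 58.95, so 59 per arm and 118 in total. This matches section 2.3 exactly and is a plain two-group comparison of means. I use n = 47 completers per arm below.

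**2. Group × time, baseline as covariate, k follow-up visits as outcomes.** The test is F with k − 1 and (94 − 3)(k − 1) degrees of freedom. Its noncentrality is λ = (n/2) × SS / [σ²(1 − ρ)], where SS is the sum of squared deviations of the visit-specific arm differences from their mean.
- Constant 0.15: SS = 0, so λ = 0 and the rejection rate is alpha, 5%, whatever ρ is and whether k is 2 or 5.
- Linear rise (0.0375, 0.075, 0.1125, 0.15, then 0.15 at month 13): mean 0.105, SS = 0.0095625, λ = 23.5 × 0.0095625 / [0.0676(1 − ρ)] = 3.324 / (1 − ρ).

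**3. Between-group tests for a constant 0.15, same model.**
- Month-12 contrast: SE = 0.26 × √(1 − ρ²) × √(2/47). At ρ = 0.3 this is 0.0512, and 0.15 / 0.0512 = 2.93.
- Group effect averaged over k visits: SE = √{0.0676 × [(1 + (k − 1)ρ)/k − ρ²] × 2/47}. At ρ = 0.3 and k = 2 this is 0.0401, and 0.15 / 0.0401 = 3.74.

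**4. Group × time with baseline as a level of time and not a covariate.** For a constant 0.15, SS = 0.0225 × k/(k + 1). With k = 5, λ = 23.5 × 0.01875 / [0.0676(1 − ρ)] = 6.518 / (1 − ρ), on 5 and 460 degrees of freedom.

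| Power at 47 per arm | ρ = 0.3 | ρ = 0.5 | ρ = 0.7 |
|---|---|---|---|
| Group × time, constant 0.15, baseline as covariate | 5% | 5% | 5% |
| Adjusted group effect, months 12 and 13 | 96% | 97.5% | 99.6% |
| Adjusted group effect, five visits | over 99% | over 99% | over 99% |
| Month-12 contrast | 83% | 89% | 97% |
| Group × time, linear rise to 0.15, baseline as covariate | 37% | 51% | 76% |
| Group × time, constant 0.15, baseline as a level, five follow-up visits | 63% | 80% | 97% |
| Same, months 12 and 13 | 68% | 83% | 97% |

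Simulation of the same cases agrees to within about two points: 5% for the constant effect (4.7% to 6.5% across runs), 96% to 100% for the group effect, 82% to 97% at month 12, 37% to 78% for the rise, and 62% to 97% with baseline as a level. The simulated ranges are the ones quoted elsewhere in this point.

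**5. A fading effect.** For 0.15 at month 12 halving to 0.075 at month 13, simulation gave group × time 23% to 44%, against 78% to 94% for the group effect.

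**The case against.** - **Baseline may be a level of time.** Listing time and group × time is common wording when it is, and the article does not settle it. Group × time is then a valid test, with 89% to 90% power for 0.15 at ρ = 0.6. If baseline is also a covariate and its interaction with time is fitted, simulation at ρ = 0.6 still gave 95% to 98%. This stands. A reader might infer that the 80% power fails on every reading; it does not. But adjustment for baseline values is what the text states, and without the covariate 80% is reached only from ρ of about 0.5.
- **A benefit need not be missed.** A reader might infer that Tele-SSE could never be shown to work under this plan. The 5% figure requires an effect that is flat across the follow-up visits. Table 1 raises difficulty until month 7 and month 13 follows the end of training, so some change is plausible and would be partly detected. This also stands.
- **The list of results is not exclusive, and an article condenses.** True, and no sentence rules out reporting a group effect. Even so, the article fixes the model and picks the effects to be tested. Those are the wrong ones for the natural reading, so this is more than missing detail. Cohen's d does not repair it, because its contrast is not given.
- **Groups are compared on QALYs** in sections 2.7.1 and 2.9. That is estimation for the cost-utility analysis. It does not supply the test of effect for the outcomes in section 2.8.
- **The EQ-5D-5L schedule is inferred** from the cost-effectiveness row. Conceded; results are given for two and for five follow-up visits, and the 5% is the same for both.

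**Conclusion.** The point holds in a limited form. Section 2.8 adjusts for baseline and names only tests that, on the natural reading, do not ask whether the arms differ. A stable 0.15 benefit could then be reported as non-significant: the rejection rate equals alpha, irrespective of the correlation, while a between-group test from the same model has at least 82% power at 47 per arm. For a changing effect the loss is partial. With baseline as a level of time and not a covariate, the stated test is valid but falls short of 80% at lower correlations. The power figures rest on assumed correlations of 0.3 to 0.7, equal between visits.

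It would be wrong to conclude that the sample size is miscalculated. The 118 reproduces exactly; the fault is that its 80% power attaches to a contrast that the analysis section leaves unnamed.

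**What to change.** Reword section 2.8. Model the follow-up visits as outcomes with group, visit, group × visit, age and baseline value, and state that baseline is not also a level of time. Name the adjusted between-group difference, with 95% confidence interval and p-value, as the test of effect for continuous outcomes. Choose in advance whether this is the difference at month 12, the end of the intervention, or the group effect averaged over follow-up. The documents do not fix that choice, and either is defensible. Tie Cohen's d to the same contrast and keep group × visit as supportive. The cost is analysis wording only: no new data, visits or participants.
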